### Confidentiality and data security

At first contact (e.g. pregnancy counselling or booking the birth) and on admission to the OU, eligible women will be given oral and written information on the study and their rights in terms of data protection and data handling. The pregnant women will be asked for their written consent regarding (a) participation in the study, (b) confidential handling of their data by authorised members of the study team and (c) use of their contact data for the follow-up data collection at 3 months postpartum. Both parents, or the respective legal guardian, will have to give their consent for the use of the infant’s data. Participants will also be given a further option of providing consent for a secondary analysis of data within the scope of bachelor’s, master’s or doctoral theses. Study participants will receive a copy of the signed informed consent while the original will remain in the OU. All data will be documented in a case report form (CRF), each of which will have a unique code to prevent identification of participants (pseudonymisation) and their allocation (to the trial arms). The list of codes identifying participants will remain in the OU.

Study participants will be informed about their rights under the European General Data Protection Regulation (GDPR), which was enacted on 25 May 2018. Participants will be informed that they can withdraw from the study at any time without giving a reason and with no disadvantage to their care. Data recorded about a participant who withdraws will be deleted at her request.

Access by unauthorised third parties to the CRFs and other data will be prevented by secure handling and storage according to national legal requirements. After the data have been validated in the OU, independent monitors appointed by the sponsor will forward the CRFs to KKS Halle by registered and insured postal delivery. KKS Halle will exclusively hold the list of code numbers and the allocation to the control and intervention groups. After data entry into a data management system and second-look data entry and query management, the paper CRFs will be stored in the medical faculty’s archive for at least 10 years according to legal requirements. After data analysis, the digital data will be securely stored on the server of the Institute of Health and Nursing Science, Martin Luther University of Halle-Wittenberg. Only pseudonymised data will be analysed, and our results will be published in aggregated form.

The lists containing study participants’ contact data will be forwarded by the monitors to the respective trial centres (Martin Luther University of Halle-Wittenberg for the eastern states and the University of Applied Sciences Sciences (*Hochschule für Gesundheit*) in Bochum for North Rhine-Westphalia), where they will be stored securely. The trial centres will use the contact information solely to send questionnaires (and reminders if necessary) to study participants at 3 months postpartum. The contact information sheets will be destroyed immediately after closure of the data collection period unless consent for secondary data analysis was given.

### Data capture and discrepancies

All data will be captured on paper-based CRFs at the OU and transferred to KKS Halle for data management, where the data will promptly be entered into a database. A clinical data management system developed for clinical trials (secuTrial®), which is compliant with good clinical practice, will be used for data entry and query management. All changes in data will be recorded by an audit trail and the data will be saved daily. Data will be electronically checked for plausibility and consistency in a multistage procedure. If there are implausible or missing data, the relevant OU will be asked to obtain any missing information and to resolve inconsistencies. The database is integrated into a general secure system with a firewall and backup system. After completion of data collection, data capture and quality checks, the database will be closed and the data transferred to the biometrician for statistical analysis.

Only after completion of the statistical analyses will the data set be transferred to the trial sponsor, who will keep securely it for 10 years based on national legal requirements.

### Statistical issues and sample size

To determine the rather modest intervention effect of an absolute increase of 5% from an estimated baseline of 74% of VB, the following were noted:The rate of CSs in low-risk pregnant women is lower than in all pregnant women, since about one third of CSs are due to multiple births, breech presentations and prematurity or are elective.The primary endpoint in this trial is VB, which also includes OVBs.In sensitivity analyses, a risk ratio (RR) of 1.20 (95% confidence interval (CI) 1.05 to 1.38; two trials, 240 women) was documented for a spontaneous VB due to increased mobility and upright body positions in the first stage, but there was no statistically significant difference for OVB [6].An RR of 1.03 (95% CI 1.01 to 1.05) was found for the likelihood of spontaneous VBs in alternative birth settings, and an RR of 0.89 (95% CI 0.79 to 0.99) for the likelihood of OVBs (8 trials; *n* = 11,202) [14].

As the RR of 1.20 (see (c) above) for a spontaneous VB was calculated based on only two trials with a total of 240 women, we decided on a more conservative increase in the probability of VBs of 5%, i.e. from a baseline of 74% to 79%, corresponding to an RR of 1.07. This takes into account that the increase is more likely to be modest in those OUs where the rate of VBs is already higher. In addition, a smaller effect may be expected due to contamination bias if the same staff care for women in both trial groups.

Using a two-sided Fisher’s exact test, a sample of 3440 women would be required to detect a change of 5 absolute percentage points (from 74% to 79%) in the prevalence of VB (primary outcome) with a power of 90% (a significance level of 5%, assuming a dropout rate of 10%). The sample size has been enlarged to 3800 women to ensure there is sufficient power if there are deviations from the planning assumptions, e.g. increased dropout rates or different baseline rates in OUs recruited to replace study sites that prematurely withdraw from study participation.

### Data analysis

Characteristics of the OUs (centres), study participants and outcomes are described separately for the intervention and control groups (depending on their distribution) using frequency tables, estimated probabilities, 95% CI, means ± standard deviations and percentiles. The analysis performed is intention to treat. In the primary analysis, the probabilities of a VB in the intervention and control groups are compared by Fisher’s exact test using a significance level of 5%. The risk difference and 95% CI are estimated. Additionally, randomised women with missing data in the primary outcome (e.g. dropouts) will be compared to the analysis set with respect to available characteristics, including statistical tests depending on their distribution (Fisher’s test, *t*-test or Wilcoxon rank sum test).

Sensitivity analyses for missing values will be performed in the full intention-to-treat population by multiple imputation, including adjustment for centre effects using logistic regression models with dependent variable VB (yes/no), random effects centre and intervention (versus control) as independent variable (reference for generalised linear mixed models [48]). A further logistic regression model will include an additional random effect of the interaction centre*intervention to adjust for possible centre effects on the intervention effect.

The following variables will be classified and included as independent variables in the logistic regression models above (with and without interaction with intervention) to investigate the role of potential clinically relevant prognostic factors which include: annual baseline rates of VBs of participating OU, age, body mass index, parity, induction of labour with allopathic medicine on admission to birthing room and fear of childbirth.

Five binary, log-normally and ordinally distributed *secondary outcomes* will be compared between the intervention and control groups by Fisher’s test, *t*-test (after a log-transformation if necessary) and Wilcoxon’s test. Multiple testing (five tests) will be adjusted by the Bonferroni method using a reduced significance level of 1%. No imputation is planned for the secondary outcomes.

All tests are two-sided unless otherwise stated. No interim analyses are planned, with the exception of a descriptive analysis to ensure safety (Section 2.11).

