## Background

### Mode of birth

The rate of caesarean sections (CSs) in Germany in 2016 [1] was higher than recommended by Betran et al. [2] despite being associated with an increased risk for maternal morbidity and mortality [3]. The average CS rate was 32.1%, with regional differences ranging from 17% to 51% [1]. Of these, 18.7% were repeat CSs with no additional medical indication whilst 30.7% had additional medical indications [1].

Of all live hospital births, 80.6% (*n* = 623,685) were singleton births at term in cephalic presentation. Of these, 75.2% (*n* = 469,195) were spontaneous vaginal births (VBs) or operative vaginal births (OVBs) [1]. In the federal states of North Rhine-Westphalia and Saxony-Anhalt in 2016, VB and OVB rates were 73.1% and 75.0%, respectively [4, 5].

In Germany, most spontaneous VBs occur in a maternal recumbent position on a birthing bed. In 2016, there were 77,123 per 100,000. Only 9616 per 100,000 are documented to have occurred in an upright or unspecified position [1]. In international studies, low-risk women in recumbent positions in the first stage of labour were more likely to have an epidural, a CS or their babies admitted to a neonatal intensive care unit [6]. Recumbent positions in the second stage of labour are associated with increased administration of opioids and oxytocin [7], a higher rate of episiotomies [7] and vaginal operative births [7, 8], and increased levels of pain [7, 8] and fatigue [9, 10].

If labour is prolonged or obstructed, there appears to be room for behavioural interventions to increase the possibility of a VB. The prevalence of prolonged or obstructed labour in Germany in 2016 was 6.5% (sole diagnosis) or 21.1% if documented alongside other diagnoses [1].

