#### Randomisation

Only after confirmation of her eligibility and after providing informed consent at admission will a woman be randomised by a midwife or obstetrician and receive an ID code, provided the intervention birthing room and a control birthing room are simultaneously available. Randomisation is ethically acceptable as the birthing environment in both trial groups enables safe midwifery and obstetric care. Individual randomisation is feasible as women usually do not have a choice of which room they will give birth in.

A detailed randomisation plan and lists have been generated by an independent statistician in advance [36], based on the participating OU’s annual baseline rates of VB in 2016. Randomisation will be stratified by units (12 OUs) and parity (two strata, 1:1 per unit). Blinding of either the participants or the attending staff is not possible.

Randomisation will be centrally controlled and concealed. In particular, randomisation will be performed online in real time using a validated dynamic web application provided by the independent Coordination Centre for Clinical Trials (KKS) in Halle (Saale). Each OU will be provided with an iPad with online access to the KKS web application, to ensure that the attending midwife or obstetrician does not need to use the hospital’s electronic devices. After noting the online assignment of the participant to one of the two study groups, the attending midwife or obstetrician will take the woman to the relevant birthing room.

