### Benefits, burden and safety

Women in labour will not be able to participate in the study if both birthing rooms required for randomisation are not available. Women with a preference for a particular birthing room will have only a 50% chance of being randomised to it. However, women do not usually get to choose their birthing room. In any case, women will receive midwifery and medical care according to hospital standards. Her partner or companion can be involved in supporting the woman in any birthing room.

There are indications of *benefits* for pregnant women assigned to the *intervention group*:- The intervention is in accordance with women’s desire for a more home-like environment for their birth. It offers options for various body positions and to move around, allows them to relax and may improve their well-being.- There is evidence that greater mobility and longer periods of being upright in labour result in a significantly decreased probability of episiotomy and epidural analgesia.- There is evidence that a VB will result in significantly improved client-centred outcomes, such as maternal satisfaction.

The following *burdens* might be experienced on being assigned to the *intervention group*:- Continuous foetal heart monitoring may be difficult to achieve in various positions, even if telemetry is used. If necessary, the beanbag, a chair or the mattress could be used for intermittent monitoring or auscultation.

The necessary equipment for women and newborns will be readily available in the event of an emergency. If foetal scalp blood sampling or an OVB become necessary, the screen or curtain can be removed from the birthing bed or the delivery bed can be wheeled into the room.

All AEs and SAEs will be documented in the CRF and validated in 100% of cases, including third- and fourth-degree perineal tears, blood loss >1000 ml, the composite indicator newborn health, serious maternal morbidity (e.g. amniotic fluid embolism) and serious obstetric complications (e.g. shoulder dystocia).

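### The primary Fisher's exact test ignores the unit and parity strata used in randomisation: valid and powered as planned, but conservative and slightly less efficient than a stratified analysis

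*Protocol article*

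**What the plan says.** **Allocation** (Protocol article, Randomisation): "Randomisation will be stratified by units (12 OUs) and parity (two strata, 1:1 per unit"), which makes 12 × 2 = 24 strata.

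**Primary analysis** (Data analysis): "the probabilities of a VB in the intervention and control groups are compared by Fisher’s exact test", at the 5% level. For the effect estimate the text says only "The risk difference and 95% CI are estimated", and no interval method is named. "All tests are two-sided unless otherwise stated".

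**Where the stratification factors enter.** The base missing-data sensitivity model has "random effects centre and intervention (versus control) as independent variable"; parity is not in it. A further model adds a random centre-by-intervention term. Parity joins the random-centre models as one of several prognostic factors (Data analysis) and as the subgroup factor (Subgroup analysis).

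**Prognostic value.** Data collection and outcome measures lists parity among the relevant prognostic factors. Statistical issues and sample size expects a smaller gain in OUs whose VB rate is already higher. No VB rate by OU or by parity is given.

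**The concern.** Stratified allocation balances the arms within each OU-by-parity stratum. If the strata differ in VB rate, this balance removes between-stratum variation from the true sampling variance of the difference between arms. A single pooled 2×2 table still counts that variation as noise. The test then rejects less often than 5% under the null and gives up some power that stratification had made available. Fisher's test is also conservative in its own right, because it is discrete.

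A little efficiency is at stake, not validity. The protocol warns that contamination and OUs with high baseline rates could shrink the effect, and a smaller effect makes a borderline result more likely. In that case the less efficient of the planned analyses would decide the trial.

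**Working it through.** **1. Reproduce the planned sample size.** Inputs from Statistical issues and sample size: 74% vs 79%, two-sided 5%, 90% power, Fisher's exact test, 10% dropout. The continuity-corrected formula for two proportions gives 1549 per arm; 1549/0.9 rounds up to 1722 per arm, or 3444 in total. Exact enumeration of Fisher's test gives 90.03% power at 1548 per arm, and 2 × 1548/0.9 = 3440. The stated figure is confirmed, and it was calculated for the pooled test.

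**2. Fisher's own conservatism.** By the same enumeration at 1548 per arm with 74% in both arms, the true size is 4.55%, which corresponds to a critical value of z = 2.00 instead of 1.96. This has nothing to do with strata.

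**3. Share of outcome variance between strata.** Assumptions, because the documents give no stratum rates: OU standard deviation s of 5 to 7 points, parity gap g of 15 to 20 points, half of the women primiparous, average 74%.

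f = (s² + 0.25 g²) / (0.74 × 0.26)

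- s = 0.05, g = 0.15: (0.0025 + 0.005625)/0.1924 = 0.042
- s = 0.07, g = 0.20: (0.0049 + 0.0100)/0.1924 = 0.077

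The true standard error is the pooled one times √(1 − f), that is 0.979 to 0.961 of it.

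**4. Type I error by normal approximation.** For pooled Fisher, 2 × [1 − Φ(2.00/√(1 − f))] = 4.1% at f = 0.042 and 3.7% at f = 0.077. Simulation of 24 balanced strata under these assumptions gives about 3.5 to 4.4%, with CMH at about 5%.

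**5. Power, 74% vs 79%.** With n per arm, SE = √[(0.74 × 0.26 + 0.79 × 0.21)/n]. This is 0.01521 at n = 1548 and 0.01448 at n = 1710. The null SE₀ uses the mean rate of 76.5%. Taking the same f in both arms:

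- Fisher: Φ[(0.05 − 2.00 SE₀)/(SE √(1 − f))]
- Stratified: Φ[(0.05 − 1.96 SE₀ √(1 − f))/(SE √(1 − f))]

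| Analysed | Fisher, approximation | Stratified, approximation | Simulation, Fisher vs CMH |
|---|---|---|---|
| 3,096 (3440 less 10%) | 90.5 to 90.9% | 91.9 to 92.8% | about 90.5% vs 92 to 93% |
| 3,420 (3800 less 10%) | 93.1 to 93.5% | 94.1 to 94.9% | about 93 to 94% vs 94 to 95% |

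**6. Splitting the gap.** Replacing 2.00 by 1.96 in the Fisher formula raises power at 3,096 from 90.5% to 91.2% (f = 0.042), so about 0.7 points are discreteness. Simulation puts this part at 0.6 to 0.8 points. The rest comes from ignoring the strata.

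**7. Confidence interval, if it is an ordinary pooled one.** Its excess width is 1/√(1 − f) − 1 = 2.2 to 4.1%, and its coverage is 2Φ(1.96/√(1 − f)) − 1 = 95.5 to 95.9%.

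**8. Wider range.** With control rates in primiparae/multiparae from 74%/74% (no OU spread) to 57.5%/90.5%, simulation at about 3,072 analysed gives Fisher 89.7% vs CMH 90.4% at one end and 91.6% vs 94.5% at the other. Fisher's type I error falls from about 4.3% to 3.0% over that range.

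**The case against.** The strongest defence is that nothing is broken. Design and analysis use the same test, the sample size reproduces, type I error stays below 5%, and power is about 93% at the planned 3800 with 10% dropout. A simple and conservative primary test is a defensible choice, and its error runs towards missing an effect rather than claiming a false one. All of this stands, and it limits the point to efficiency.

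Four stronger readings are tempting, but the document does not support them:

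- **A reader might infer that the trial is underpowered.** It is not. The loss is relative to another test, not to the plan.
- **A reader might infer that centre and parity are never adjusted for together.** Random centre also appears in the centre-by-intervention, prognostic-factor and subgroup models, and parity is in the last two. What is missing is an analysis with both factors at primary or base-sensitivity rank.
- **A reader might infer that the reported interval is certainly too wide.** The interval method is not named, so this holds only if an ordinary pooled interval is used.
- **A reader might take** "with regional differences ranging from 17% to 51"% (Mode of birth) **as the spread between trial OUs.** That is the caesarean rate across regions for all births. It is not VB among term singleton cephalic births in the participating units. The same section gives VB rates of 73.1% and 75.0% for two of the participating states, which do not bound the OU spread either.

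The size of the effect therefore rests on assumed stratum rates. The direction does not: it follows from stratified allocation whenever the strata are prognostic, and the protocol says that it expects them to be.

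**Conclusion.** The point holds as a modest matter of efficiency. The pooled Fisher test is valid and delivers its planned power. It is conservative, with a true type I error of about 3.5 to 4.4%, and its power is about 1 to 2 points below an analysis by the randomised strata. Somewhat less than 1 point of that gap would remain even if the strata did not differ at all. These figures rest on an OU standard deviation of 5 to 7 points and a parity gap of 15 to 20 points, neither of which is in the document. Smaller differences shrink the gap towards the discreteness part alone, and larger ones widen it to about 3 points.

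**What to change.** Before any unblinded data are seen:

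- Make the primary test a CMH test stratified by OU and parity, and report the Mantel-Haenszel risk difference with its 95% CI. An equivalent is a logistic model with OU and parity and a standardised risk difference.
- Name the interval method.
- Keep the pooled Fisher test as a sensitivity analysis.
- Add parity to the base random-centre sensitivity model, which at present has centre only.

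The cost is wording in the protocol and analysis plan. Both factors are known at randomisation, so no further women or data are needed. The sample size can stay as it is, since the stratified test has at least the power of the pooled one in every setting examined. With 3,096 analysed there are about 3,096/24 = 129 women per stratum on average, enough for CMH to behave well.

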### Data collection and outcome measures

The four data assessment points will be on admission (*t*_0_), during labour in the birthing room (*t*_1_), on the postnatal ward before discharge from hospital (*t*_2_), and at 3 months postpartum as a follow-up (*t*_3_) (Table 1). For the follow-up, the participants are asked to provide their contact data and, if possible, the contact data of a second person.

Baseline information (*t*_0_), including psychosocial and obstetric data, will be obtained from eligible and consenting participants prior to randomisation. The baseline data include relevant prognostic factors (independent variables), such as age, body mass index, parity, whether labour is induced and previous CSs. Additionally, the highest educational qualification, migrant background, number of pregnancies, current gestation, any premature rupture of membranes and time of admission to OU will be noted.

The attending midwives and obstetricians will document primary, secondary and other endpoints during active labour (first and second stages) and after the birth. The primary outcome is VB (binary variable), including both spontaneous VB and OVB. Key secondary endpoints, evidence-based and clinically highly relevant, are epidural analgesia, episiotomy, third- and fourth-degree perineal tears (all binary), and maternal self-determination (continuous variable). The latter is the only variable explaining variance in satisfaction with the birth experience [19], and will be assessed by the validated Labour Agentry Scale [37]. Since there is no German version, the 10-item scale will be translated and culturally adapted. It will be validated in a relevant sample of pregnant women living in Germany during the preparation phase of the trial.

Since previous trials used heterogeneous endpoints, an additional key secondary outcome, the composite indicator critical outcome of newborn at term (binary), will be calculated (based on Apgar at 5 min, umbilical artery pH and umbilical artery base excess). Nationally, these outcomes constitute the indicator (ID 1059) for term newborn in a critical condition [1]. Missing data for these outcomes are unlikely, as they constitute routine data.

Other endpoints that will be assessed are the following:

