*Binary variables*: Artificial rupture of membranes, oxytocin labour augmentation, use of any analgesia, mode of foetal heart monitoring, prolonged second stage (>30 min or >60 min), blood loss >1000 ml, first- and second-degree perineal tears, other tears to the genital region, maternal transfer to an intensive care unit, maternal death, initiation of breastfeeding, joint discharge of mother and infant from postnatal ward, any diagnosis of health risks in the infant, seeking medical help from a paediatrician or readmission to hospital.

*Nominal variables*: First, second, and third most frequent maternal body positions during labour and birth (as estimated by the midwife), mode of birth, serious adverse events (SAEs; e.g. shoulder dystocia, placental abruption, foetal acidosis, prolapsed chord, HELLP, etc.), use of the delivery bed and breastfeeding.

*Ordinal variables*: Fear of birth (six items [43–45]), adverse events (e.g. pain associated with the perineum, sutures, urination and defecation, breastfeeding, etc.), self-rated health and postnatal depression (Edinburgh Postnatal Depression Scale [38, 46]).

*Continuous variables*: Gestational age, expectations of birth, severe labour pains, experience of birth, subjective usefulness of the equipment in the birthing room, helpfulness of the companion, birth weight, length of stay in the birthing room and on the postnatal ward, infant regulation disorders (relating to crying, nutrition or sleeping) and duration of breastfeeding. Early mother–child bonding will be assessed with the Postpartum Bonding Questionnaire [47],

Additionally, items pertaining to the costs of the intervention and health-care utilisation costs after discharge from hospital (e.g. frequency of medical consultations and use of medication) and money spent on formula or breastfeeding aids will be assessed by a health economic evaluation [35]. Study participants will also be asked to indicate how much they would be willing to pay for an alternative birthing room if they were given the option between a standard or an alternative birthing room.

After conclusion of the recruitment period, midwives and obstetricians will be asked about their experience of and job satisfaction pertaining to the care they provided in the intervention and control birthing rooms (staff-related outcomes).

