#### Subgroup analysis

Subgroup analyses are planned for two parity strata (primiparae and multiparae) and the primary outcome (VB). Subgroup analyses will be performed with respect to the primary outcome using logistic regression analyses. The primary outcome is the dependent variable. Centres are random effects. Independent variables are intervention versus control, subgroup indicators, and the interaction between subgroup and intervention/control.

An additional model including previous CSs as a further independent variable will be fitted in the subpopulation of multiparae only.

The whole analysis will be repeated as a per protocol analysis on the subpopulation after exclusion of participants with protocol violations (expected to be about 10%) or missing values in the primary outcome.

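### Previous caesarean is recorded at baseline and named as prognostic, yet it is left out of the adjusted models for all women; a three-level parity factor would carry it at almost no cost

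*Protocol article*

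**What the plan says.** All references are to the protocol article.

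- **Data collection and outcome measures** describes what is collected at t0, before randomisation: "The baseline data include relevant prognostic factors (independent variables), such as age, body mass index, parity, whether labour is induced and previous CSs".
- **Data analysis** defines the primary comparison without covariates: "In the primary analysis, the probabilities of a VB in the intervention and control groups are compared by" Fisher's exact test, with a risk difference and 95% CI. It then sets out logistic models with a random centre effect as sensitivity analyses. Of these it says: "The following variables will be classified and included as independent variables in the logistic regression models above", with and without interaction with the intervention. The list is the unit's annual baseline VB rate plus "age, body mass index, parity, induction of labour with allopathic medicine on admission to birthing room and fear of childbirth".
- **Subgroup analysis** is the only place where previous CS enters a model: "An additional model including previous CSs as a further independent variable will be fitted in the subpopulation of multiparae only".
- **Data collection and outcome measures** also introduces a list with "Other endpoints that will be assessed are the following". Among its ordinal variables is "Fear of birth (six items" in number), with no assessment time attached.
- **Participants and eligibility criteria** does not list previous CS as an exclusion. **Randomisation** stratifies by unit and parity only.

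**The concern.** Of the five prognostic factors that the article names as examples at t0, four go into the models for all women and one, previous CS, does not. Women with a previous CS who plan a VB can enrol, and randomisation does not balance for it. So neither the design nor the full-population adjustment deals with it. In those models the category multiparous mixes women with and without a previous CS, whose chance of a VB may differ.

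What is at stake is the quality of the secondary adjusted estimates, to which readers will turn to see whether the unadjusted result is robust. If previous CS happens to fall unevenly between arms, the models meant to address such imbalance will not correct it in the full population.

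A second, smaller matter concerns the same covariate list. Induction is a t0 item in one section, but in Data analysis it is tied to admission to the birthing room, which the Intervention section places after randomisation. Fear of birth is both a covariate and a listed endpoint. In an unblinded trial a covariate should be fixed before allocation, and the text should say so.

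**Working it through.** **1. The plan's own sample size, to see whether this point touches it.** Inputs from Statistical issues and sample size: 74% vs 79%, two-sided 5%, power 90%, dropout 10%.

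n per arm = [1.960·√(2·0.765·0.235) + 1.282·√(0.74·0.26 + 0.79·0.21)]² / 0.05² = 1510, or 1549 with continuity correction. In total 2·1549 = 3098, and 3098/0.90 = 3443, against 3440 stated. Exact Fisher power is 90.3% at 1548 per arm (3440 less 10%) and 92.8% at 1710 per arm (3800 less 10%). The figure reproduces. It rests on the unadjusted test, so no choice of covariates alters it.

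**2. Covariate lists side by side.**

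| Variable | Named prognostic at t0 | In models for all women |
|---|---|---|
| Age | yes | yes |
| BMI | yes | yes |
| Parity | yes | yes |
| Induction | yes | yes, worded as on admission to the birthing room |
| Previous CS | yes | **no** (multiparae-only model) |
| Fear of birth | not listed | yes |
| Unit VB rate | not an individual variable | yes |

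**3. Size of the previous-CS effect.** The documents give neither the share of participants with a previous CS nor the VB gap. Assumed: share p = 10–15%, gap d = 15–25 percentage points.

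*Share of outcome variance* = p(1−p)d² / (0.74·0.26):
- p = 0.10, d = 0.15: 0.002025/0.1924 = 1.1%
- p = 0.10, d = 0.25: 0.005625/0.1924 = 2.9%
- p = 0.15, d = 0.25: 0.00797/0.1924 = 4.1%

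This is for previous CS alone, not in addition to parity.

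*Chance imbalance* with 1900 per arm: SD of the difference in share = √(2p(1−p)/1900).
- p = 0.10: √(0.18/1900) = 0.97 points
- p = 0.15: √(0.255/1900) = 1.16 points

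*Shift in risk difference for a one-SD imbalance* = SD·d:
- d = 0.25: 0.97·0.25 = 0.24 and 1.16·0.25 = 0.29 points
- d = 0.15: 0.97·0.15 = 0.15 and 1.16·0.15 = 0.17 points

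For scale, the standard error of the risk difference at 1900 per arm is √((0.1924 + 0.1659)/1900) = 1.37 points, so the larger shifts are about a fifth of one standard error. Stratification by parity makes the true SD slightly smaller than this formula gives. The gap within multiparae may differ from the overall gap assumed here.

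**4. Effect on the odds ratio.** The planned 74% vs 79% is a marginal OR of (0.79/0.21)/(0.74/0.26) = 1.32. With 5–12% previous CS and an OR of 0.1–0.4 for VB (both assumed), the OR conditional on previous CS is 1.33–1.39. That is a change in what is estimated, not a correction of bias.

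**The case against.** The strongest reply is that these models are not the trial's answer. The article presents them as sensitivity analyses and as a look at prognostic factors; the confirmatory comparison is unadjusted. Leaving a baseline covariate out does not bias a randomised comparison, and the confidence interval already reflects ordinary chance imbalance. Previous CS is also not ignored: it is modelled in multiparae, the group in which it ordinarily varies. The wording that introduces the covariate list can be read as not exhaustive. All of this stands, and it limits the weight of the point. It does not explain why a factor that the trial names as prognostic and already holds should be missing from the models for all women, when a combined factor copes with primiparae having none.

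A reader might also infer stronger things that the documents do not support:

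- *That fear of birth is measured after allocation.* Being listed among endpoints does not show this. The same list holds gestational age, and psychosocial data are collected at t0. The time point is simply not given.
- *That induction is a post-randomisation value.* It is among the t0 data, and status on entering the room can hardly have been changed by the room. The two wordings only need to be aligned.
- *That the 18.7% repeat-CS figure in the Background shows how common or strong the factor is here.* It covers all German caesareans, whereas this trial enrols women in active labour who plan a VB.
- *That classifying age and BMI is an error.* No cut-points are given, and coding is ordinary analysis-plan detail. Equal groups of 2, 3, 4 or 5 would keep about 64%, 79%, 86% or 90% of the explained variance of a normal covariate with a linear effect, so continuous terms are an optional gain.

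**Conclusion.** The point holds as an inexpensive improvement to the secondary analyses. Previous CS belongs in the full-population adjusted models and is missing from them, so those models pool two kinds of multiparae and cannot correct a chance imbalance in this factor across all women. The primary Fisher test, the sample size of 3800 and its power are unaffected, and no stated figure is wrong.

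The gain is modest and its size rests on assumptions. With 10–15% prevalence and a 25-point VB gap, a one-SD imbalance shifts the risk difference by about 0.24–0.29 points; with a 15-point gap, by 0.15–0.17. A reader might go further and cite a 2-point imbalance, which at a 25-point gap shifts the risk difference by 0.02·0.25 = 0.5 points, a tenth of the target effect. That imbalance is about 2/0.97 = 2.1 or 2/1.16 = 1.7 SD (two-sided chance roughly 4% or 8%), so it is an upper-end case and not the expected one. Nor should the variance share of 1.1–4.1% be turned into a number of women lost, because power does not depend on these models.

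**What to change.** In the logistic models of the Data analysis section:

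1. Replace two-level parity by a three-level factor: primiparous; multiparous without previous CS; multiparous with previous CS. The planned parity subgroup analysis and the multiparae-only model can stay as they are.
2. State that only values of induction and fear of birth obtained at t0, before randomisation, enter as covariates. Align the induction wording with the t0 list, and give the assessment time of fear of birth. If fear of birth is not collected at t0, it should not be used for adjustment.
3. Optionally, keep age and BMI continuous.

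The cost is a few sentences in the analysis plan, settled before the data are analysed. Parity, previous CS and induction are already t0 items. For fear of birth this cannot be confirmed, because the case report form is not shown. No change to recruitment, sample size or the primary analysis is needed.
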